### Analysis

The data will be analyzed using SCED methods and linear mixed-effects models to capture both individual-level changes and group-level effects over time.

### SCED analysis

The items from the weekly measurements will be displayed in graphs and inspected visually, which is standard practice in SCED [32]. The graphs will be evaluated regarding direction and slope of change in the data, i.e., the trend, as well as onset, that is, when change occurs. This will be done separately for each participant.

When using SCED it is recommended to supplement the visual analysis with calculating the effect size in order to provide standardized and reliable indices. We will use Nonoverlap of All Pairs (NAP) in which each data point in Phase B (intervention) is compared with each data point in Phase A (baseline) [53]. NAP effect sizes of 0-0.65, 0.66–0.92, and 0.93-1.0 corresponded to small, moderate, and large effects based on expert visual judgment [53].

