### Materials

Primary outcomes are assessed through the parent SCED data collection, while the secondary outcomes are assessed through child SCEDs, pre/post-measures and the child’s medical records.

Primary outcomes.

Child behavior problems.Parental self-efficacy.Parental stress.

Secondary outcomes.

Child mental health problems.Parents’ mental health.Parents’ quality of life.Goal attainment and client satisfaction.Child medical data.Children’s positive and negative experiences of family life.

In the current study, data are collected from five sources:

Parent weekly short measures.Validated questionnaires at pre-, post- and 3-month follow-up (T1, T2, T3).Forms on goal, goal attainment and client satisfaction with the intervention.Data from the child’s medical records.Child weekly short measures.

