#### Parent weekly short measures

The short measure that parents will answer weekly was developed specifically for this project. It contains 25 questions on children’s behaviors, on parents’ self-efficacy and on parents’ perceived stress. The questions on children’s behaviors are based on the validated Eyberg Child Behavior Inventory [39], the questions on self-efficacy are from the validated Me As a Parent questionnaire [40] and the questions on stress are from the Parental Stress Scale [41]. The questions were modified together with the project’s Parent Council (parents who had previously participated in the Everyday Life and Parenting) as well as with the Clinical expert group (consisting of a child psychologist and a special education teacher who delivers the intervention) to fit the context. Basing the questions on validated forms increases the reliability of the results.

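### The three primary outcomes are constructs, but the SCED analysis graphs the individual items of a 25-question measure and gives no step from items to constructs

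*Protocol article*

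**What the plan says.** Under Materials, the article lists child behavior problems, parental self-efficacy and parental stress as the primary outcomes and assigns their source: "Primary outcomes are assessed through the parent SCED data collection, while the secondary outcomes are assessed through child SCEDs, pre/post-measures and the child’s medical records". These are the constructs of Objectives 1 and 2.

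Under Parent weekly short measures, the instrument is described as new: "The short measure that parents will answer weekly was developed specifically for this project". On its content: "It contains 25 questions on children’s behaviors, on parents’ self-efficacy and on parents’ perceived stress". The questions are adapted from three validated scales. The number of questions per construct is not given.

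Under SCED analysis, the unit of the visual analysis is named: "The items from the weekly measurements will be displayed in graphs and inspected visually, which is standard practice in SCED". Trend and onset are then judged, and the level is the individual: "This will be done separately for each participant". NAP supplements the visual reading. It is defined so that "each data point in Phase B (intervention) is compared with each data point in Phase A (baseline", without saying whether a data point is one item or a score. NAP values up to 0.65 are labelled small, 0.66 to 0.92 moderate, and 0.93 and above large.

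**The concern.** The objectives are stated for constructs, while the only unit named for the primary visual analysis is the item. Nothing in the article connects the two. A parent will have several item graphs for child behavior, several for self-efficacy and several for stress, and these need not agree. There is no rule for which graphs, or what combination of them, answer Objective 1 or Objective 2 for that parent.

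Two things are at stake. First, with several items per construct, the chance that at least one looks improved when nothing has changed is much higher than for a single series, and the choice of which item to report would be made after seeing the graphs. Second, if the intervention moves all items of a construct together, each item shows the change less clearly than their sum does, so the same effect can fall in a different NAP band depending on the unit chosen.

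**Working it through.** The article gives no figure that depends on the choice between items and scores, so there is none to reproduce. Its sample sizes are unaffected.

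**Count of series.** Inputs: 25 questions (Parent weekly short measures), 3 primary constructs (Materials), 15 retained parents (Participants).
- By item: 25 x 15 = 375 series.
- By construct: 3 x 15 = 45 series.

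This count needs no assumption beyond the document's own numbers.

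**Weeks per parent.** From Procedure, total length minus baseline is 15 - 4 = 11, 18 - 7 = 11 and 21 - 10 = 11. Each parent therefore has 4, 7 or 10 baseline points and 11 later points.

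**NAP.** NAP = (pairs in which the later point is better + 0.5 x tied pairs) / (baseline points x later points). The numbers of pairs are 4 x 11 = 44, 7 x 11 = 77 and 10 x 11 = 110.

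**Simulation, as an illustration.** Assumptions that the article does not give: 8 items per construct, normal latent ratings rounded to a 1-5 scale, within-week correlation between items of 0.2 to 0.4, no autocorrelation. The ranges below cover both correlations and all three baseline lengths.

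| Scenario | By item | By construct sum |
|---|---|---|
| No change: one given series reaches 0.66 | about 9-17% | about 11-18% |
| No change: at least one of the 8 items (or the one score) reaches 0.66 | about 42-65% | about 11-18% |
| Uniform 0.5 SD shift: mean NAP | about 0.63 (small band) | about 0.69-0.74 (moderate band) |
| 2 of 8 items shift by 1 SD: reaches 0.66 | about 77% for a shifted item (7-week baseline) | about 31-42% |

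The first row shows that an item is no more error-prone than a sum when nothing changes. The second shows the cost of having eight of them. The third shows dilution of a shared effect. The fourth shows that the advantage reverses when the change is confined to a few items.

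Ties on a coarse scale contribute little: with a 0.5 SD shift, mean item NAP is about 0.63 on five points and about 0.64 on a continuous scale.

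**The case against.** The strongest objection is that this is a condensed article. A scoring key for the weekly measure may sit in a fuller protocol or analysis plan, the questions are already described by construct, and silence on scoring is not a fault. That is right as far as the key goes. It does not remove the point, because the article makes a positive statement that items are what is graphed and inspected, and this does not match outcomes defined as constructs. The full validated scales given before, after and at follow-up do not close the gap either, since Materials makes them secondary.

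The other objections limit the point, and they stand:
- A reader might infer that the whole primary analysis is run item by item. The text fixes the item level for the graphs only; for NAP the unit is open. The NAP results above are therefore conditional on NAP being applied to items.
- A reader might infer that single noisy items are taken as the verdict on a construct. No section says so, the article reports no item reliability, and per series an item does no worse than a sum under no change.
- A reader might infer that a truly improving parent will generally show worsened items. That depends on effect size. At 0.5 SD the lowest of 8 item NAPs averages about 0.45-0.48 with a 7-week baseline, barely under 0.5. At 1.0 SD it is about 0.58-0.60.
- Summing helps only if the effect is shared. The Design section chooses SCED partly because the group is heterogeneous, so item-specific change is plausible.

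**Conclusion.** The point holds in this form: the primary outcomes are three constructs, the stated unit of the primary visual analysis is the item, the unit of NAP is open, and no rule leads from items to constructs. The size that rests on the document alone is 375 item series against 45 endpoint series. The size in terms of NAP is illustrative and rests on the assumed 8 items, five-point scale, correlation of 0.2 to 0.4 and independence between weeks: about 42-65% against 11-18% for an apparent moderate effect somewhere in a construct under no change, and a move from the small to the moderate band under a uniform 0.5 SD shift.

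The documents do not show that Objectives 1 and 2 cannot be answered. They show that the series that answer them have not been named. This should be corrected before the weekly data are analyzed.

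**What to change.** Under SCED analysis, state that one score per construct is the primary series for each parent, for both the graphs and NAP. For each of the three scores, name the questions that enter it, how they are combined, and which direction means improvement. Keep the item graphs as supplementary description.

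The cost is a sentence or two and a short scoring table. No new data are needed, no sample-size figure changes, and the number of primary graphs falls. The statement has to be fixed before the weekly series are examined; chosen afterwards, it would not remove the selection problem.

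The downside is that a change confined to a few items is diluted in the score, as the 2-of-8 scenario shows. The supplementary item graphs would still display it, but as description and not as the answer to a primary objective.

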### The group-based parenting intervention Everyday Life and Parenting

The Everyday Life and Parenting program targets parents of children aged 2–6 years with subclinical levels of NDDs and behavioral problems. These children are referred by child psychologists at the Uppsala Region’s child pediatric outpatient clinic. Families access the intervention through routine care triage, either from the waiting list or via recommendation by their consulting psychologist.

The Everyday Life and Parenting intervention consists of four modules. The intervention is theoretically based on social-learning theory [34] including ABA [35], the ICF framework and theory on emotion regulation [36, 37].

Three of the intervention modules include key components from the most effective parenting programs targeting behavior problems in children [24], including positive reinforcement techniques, relationship enhancement techniques and reframing unhelpful cognitive perceptions about the child, as well as emotion regulation knowledge and techniques. The fourth module is based on ABA and teaches a range of antecedent strategies [26, 35], such as how to organize the physical environment, how to use visual aids such as schemes of daily routines and time timers, and how to use high-probability request techniques. Furthermore, the modules include teaching parents general analytical and learning principles for teaching new skills or dealing with problem behaviors. In addition, parents are taught how to adapt activities and demands to the individual child, based both on his/her strengths, and on cognitive and adaptive abilities. Parents also practice reflecting on their own emotions, cognitions and abilities in order to find ways of adjusting and adapting to improve their own and their child’s well-being. This holistic approach to the child’s and the parents’ functioning is in line with the ICF framework. The delivery format of the intervention is also based on well researched components [38] and includes providing psychoeducation; discussions; formulating goals and goal attainment; homework assignments and peer support. Each module lasts 3 h and the intervention is given every other week for 8 weeks.

Depending on the parents’ preferences, the intervention is delivered either entirely on-site or digitally. In the digital option, the first session is on-site to allow parents to get to know each other. The other sessions are digital.

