### Procedure

Parent weekly measures will be collected via telephone by research assistants, with responses entered into REDCap. Data collection spans 15, 18, or 21 weeks, depending on the participant’s baseline length (4, 7, or 10 weeks). Pre-, post-, and 3-month follow-up questionnaires will also be distributed via REDCap, with pre-measures sent before baseline and post-measures after the intervention. Goal setting, goal attainment, and client satisfaction forms will be sourced from the Everyday Life and Parenting materials.

Child health data will be obtained through the Uppsala Region’s procedure for accessing research data from the electronic medical record system Cosmic. Child weekly measures will be sent digitally via REDCap and completed during the same weeks as the parent measures.

Intervention fidelity will be assessed through a checklist completed by course leaders after each module, indicating which session elements were completed.

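### The NAP bands give a 'small effect' label to participants who did not change or got worse, because the lowest band runs from 0 rather than from the chance value of 0.50

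*Protocol article*

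**What the plan says.** Under Materials, the protocol article ties its primary outcomes (child behavior problems, parental self-efficacy, parental stress) to the weekly parent series: "Primary outcomes are assessed through the parent SCED data collection".

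Under SCED analysis, those series are first graphed and judged by eye for each participant, including the direction and slope of change. NAP is then added as the effect size, in which "each data point in Phase B (intervention) is compared with each data point in Phase A (baseline". The interpretation follows: "NAP effect sizes of 0-0.65, 0.66–0.92, and 0.93-1.0 corresponded to small, moderate, and large effects based on expert visual judgment". The bands are attributed to a cited source. The section gives no chance value and has no class for no change or for worsening.

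Under Procedure, the phase lengths are given: "Data collection spans 15, 18, or 21 weeks, depending on the participant’s baseline length (4, 7, or 10 weeks" (weeks). The intervention section adds that "the intervention is given every other week for 8 weeks".

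**The concern.** The labels small, moderate and large only make sense if a higher NAP means more improvement. On that orientation the scale has a natural zero at 0.50, and everything below it points to harm. A band from 0 to 0.65 runs straight through that zero. Read as printed, every participant is given an effect label, including one whose every intervention week was worse than every baseline week.

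What is at stake is the reporting of the primary outcomes. NAP is the one standardized number planned for the weekly data, and a results table that follows these bands could list small effects for families in whom nothing changed or matters got worse. The moderate band has a related weakness: with as few as four baseline weeks, NAP varies enough by chance to reach 0.66 fairly often.

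**Working it through.** The bands are a cited convention, not a figure derived from the trial's inputs, so there is nothing to reproduce. The check starts from the definition of NAP.

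**Inputs**
- Bands: 0–0.65, 0.66–0.92, 0.93–1.0 (SCED analysis).
- Baseline points: nA = 4, 7 or 10 (Procedure).
- Later points: 15 − 4 = 18 − 7 = 21 − 10 = 11 (Procedure). If Phase B means only the intervention weeks, nB = 8 (intervention section). The protocol does not say which, so both are shown.
- Assumptions: improvement-oriented scoring, ties counted as half, independent weeks and, for the null distribution, no ties.

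**Step 1: fixed points.** NAP = (improved pairs + 0.5 × tied pairs) / (nA × nB).
- Every score identical in both phases, 4 and 11 weeks: (0 + 0.5 × 44)/44 = 0.50. Printed label: small.
- Every later point worse than every baseline point: 0/44 = 0.00. Printed label: small.
- The part of the lowest band on the worsening side is 0.50/0.65 = 77% of its width.

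**Step 2: spread under no effect.** Mean 0.50; SD = √[(nA + nB + 1)/(12 nA nB)]. With nB = 11:
- nA = 4: √(16/528) = 0.174
- nA = 7: √(19/924) = 0.143
- nA = 10: √(22/1320) = 0.129

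**Step 3: labels under no effect**, from the exact Mann–Whitney distribution of NAP = U/(nA nB):

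| nA | nB | Below 0.50 | Moderate or above, NAP rounded to 2 decimals | Moderate or above, unrounded |
|---|---|---|---|---|
| 4 | 11 | 47.5% | 20.6% | 17.1% |
| 7 | 11 | 50.0% | 14.3% | 14.3% |
| 10 | 11 | 48.6% | 11.2% | 11.2% |
| 4 | 8 | 46.7% | 23.0% | 18.4% |
| 7 | 8 | 47.8% | 16.8% | 16.8% |
| 10 | 8 | 48.3% | 13.7% | 13.7% |

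Rounding matters only for the 4-week baseline. There 29/44 = 0.659 (or 21/32 = 0.656) falls in the gap between 0.65 and 0.66 and becomes moderate only after rounding. The remaining null series, 79%, 86% and 89% for nB = 11 with rounding, are labelled small.

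**Step 4: labels under true worsening.** For normal scores with a shift of d SD, the expected NAP is Φ(d/√2). Simulation with nB = 11 (20,000 series per setting) gives:

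| Shift | Expected NAP | Labelled small (range over nA = 4, 7, 10) |
|---|---|---|
| −0.5 SD | 0.36 | 95–99% |
| −1 SD | 0.24 | 99–100% |
| −2 SD | 0.08 | 100% |

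**The case against.** The strongest reply is that the band sentence is descriptive and sourced. It does not say that participants will be counted by label or that small means benefit, and the source may treat its lowest band as weak or no effect. A NAP of 0.50 or 0.20 also shows the reader what happened. The number can express no effect or deterioration; only the label cannot. Visual analysis covers direction for each participant. The same three constructs are also analysed with mixed models on the pre, post and follow-up questionnaires, and ECBI change has unchanged and deteriorated classes. These points stand, and they limit the harm. They do not alter the NAP labels: the visual judgement is not tied to them, and the questionnaire analyses sit outside the weekly series that define the primary outcomes.

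Two stronger readings are tempting, and the protocol does not support them.
- A reader might infer that chance labels multiply over the items of the weekly form ("It contains 25 questions"). The text says "The items from the weekly measurements will be displayed in graphs and inspected visually", which concerns graphs. It does not say whether NAP is computed per item or per score. Ties on rating items also tend to lower the chance rate. With 4 and 11 weeks it was 17–19% for 5- or 7-level items, 15–16% for 3-level or skewed items, and 10% when 80% of answers are one value. The response format is not given.
- A reader might also want every label withheld unless the interval excludes 0.50. That turns a descriptive index into a significance test per participant, which is a preference and not a correction.

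An interval is a detail that an article may leave to an analysis plan, so its absence is not itself the fault. It is proposed below because the chance rates make the labels hard to read without one.

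**Conclusion.** The concern holds in this form: the printed scale mislabels null and worsening participants on the weekly primary-outcome data. That follows from the protocol's own pairwise definition and needs only improvement-oriented scoring. About half of null series (47–50%) lie below 0.50 and would still be called small, as would nearly all series with a clear worsening.

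The chance rate for moderate or above is secondary and rests on more assumptions. It is about 17–21%, 14% and 11% for 4-, 7- and 10-week baselines with 11 later weeks, and about 18–23%, 17% and 14% with 8. Both sets assume independent, untied scores. An assumed lag-1 autocorrelation of 0.3 raises the 11-week figures to about 23–26%, 21% and 18%; ties lower them. Neither moves the no-change value away from 0.50.

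This should be fixed before results are seen. It is not a fatal flaw, since no sample size or stated decision rule depends on the bands.

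**What to change.** Amend the SCED analysis text as follows.
- State the scoring direction for each outcome, so that a higher NAP means improvement, and state that 0.50 is the chance value.
- Report values near 0.50 as no effect and values below 0.50 as deterioration. Use small, moderate and large only above 0.50.
- Report NAP, or its chance-corrected form 2 × NAP − 1 (0 for no change, negative for worsening), for each participant with a confidence interval.
- Say which weeks make up Phase B, since 8 and 11 give different chance rates.

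No new data, visits or participants are needed. The cost is wording, and fewer participants will be described as showing an effect.

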### Reliable change

To obtain a picture of whether changes in intensity and frequency of child behavior problems (ECBI) are both reliable and clinically significant, we will classify children as recovered, improved, unchanged or deteriorated. This will be done by incorporating both a measure of whether the change in scores is larger than what is expected due to measurement error of the tool i.e., statistical significance (Reliable Change Index - RCI) as well as the participant’s shift from a clinical state to a non-clinical state i.e., clinical significance (Clinically Significant Change– CSC) [54]. This is calculated for each individual based on pre- and post-data, and presented as percentages (percentage of children who were classified as recovered, improved, unchanged and deteriorated). We will also conduct sub-group analysis comparing girls and boys. Even though the sample will be too small for detecting small to medium effects in sub-group analyses, including such analyses will enable meta-analyses to do so.

### Mixed-effects models analysis

For the data collected at pre-, post-, and 3-month follow-up using standardized questionnaires, linear mixed-effects models will be employed to analyze changes over time in key outcome measures. These measures include child behavior problems (ECBI), child mental health problems (SDQ), parental self-efficacy (MaaP), parental stress (PSS), and parents’ mental health (GHQ-12). Mixed-effects models are appropriate for repeated measures data as they account for within-subject correlations and can handle missing data. This approach allows for the inclusion of all available data, maximizing statistical power even if some participants have missing data at one time point [55, 56].

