Early interventions targeting children with subclinical NDDs and EBP are both recommended and wanted [20–24]. Parenting interventions have been shown to be among the most effective early interventions for improving children’s mental health and reversing negative child outcomes There are many evidence-based parenting programs targeting typically developing children and the vast number of scientific studies of these programs have made it possible to investigate the components that are most effective in reducing child EBP [24]. However, with a few exceptions, these standard programs do not entail specific strategies or approaches designed for and adapted to children with a disability [25]. Interventions targeting parents of children with disabilities often utilize applied behavior analysis (ABA) to address specific behavior or skills training to decrease maladaptive behavior and improve communication and socialization [26]. One important focus is on antecedent strategies which are used to create conditions that prevent the problem behavior before it occurs [26, 27]. Focusing on adapting and adjusting the environment and strategies to enhance the child’s functionality in everyday life in order to improve outcomes also aligns with the World Health Organization’s International Classification of Functioning, Disability and Health (ICF) framework [28]. The ICF proposes a biopsychosocial framework that stresses the interaction between personal, social and environmental factors to find supportive solutions with the aim of improving well-being and quality of life [29]. In addition to specific strategies taught, the effect of all parenting group interventions also depends on parents completing programs [30]. This in turn is influenced by the group itself and parents stress the importance of meeting other parents with similar experiences to have a sense of belonging, to share experiences and feel safe talking and to support each other [21, 30, 31]. A qualitative interview study with parents of children with subclinical NDDs demonstrated that these parents longed to meet other families with similar difficulties [21].

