## Methods

### Design

This study employs a prospective, longitudinal design, utilizing repeated assessments to observe changes in key outcome measures from pre- to post-intervention, with follow-up assessments conducted to evaluate the sustained effects over time. The study will run from August 2024 to December 2025. It combines two distinct yet complementary approaches. Firstly, a multiple baseline single case experimental design (SCED) is employed across participants, which permits a detailed analysis of individual responses to the intervention over time and a nuanced understanding of behavioral change at the participant level. This design is useful when testing the effect of an intervention in a heterogenous group of patients or when examining a known intervention for patients other than those it was originally designed for [32]. Secondly, a traditional pre-, post- and follow-up assessment using standardized questionnaires is conducted to capture broader intervention effects across the participant group, evaluating changes in key outcome measures over time. Collectively, these methods provide both detailed case-specific insights and generalizable findings.

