### Participants

The target population is children aged 2–6 years with subclinical levels of NDDs and behavioral problems and their parents. The children have been referred to child health psychologists at the child pediatric outpatient clinic in Uppsala Region and offered the parenting group intervention Everyday Life and Parenting. To be eligible for the project, the parents must attend the intervention and be able to fill in questionnaires and answer weekly measurements in Swedish. Children aged 4–6 years whose parents consent to participate in the project will be invited to participate. No other inclusion or exclusion criteria will be applied.

According to the SCED standard, at least three, preferably five, participants should be included in each baseline condition [32]. The goal in our study is to retain 15 parents and 15 children as participants, i.e., 5 parents and 5 children in each of the three baseline conditions. To take into account an expected drop-out of about 10–20% we will need to recruit about 18 parents and 18 children [33]. This is deemed to be more than sufficient to be able to make detailed SCED analyses.

In terms of pre-, post- and follow-up assessment, we want to be able to detect relatively small effect sizes. To be able to detect an effect size of 0.35 with an alpha of 0.05 and power of 80%, we will need at least 54 participating parents. If we assume a 20% attrition rate, 70 participants will need to be recruited. These results can be compared to randomized studies on similar populations.

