Groups of Everyday Life and Parenting start four to six times every term. Each group includes parents from up to 10 families, i.e., in total 20 parents. Both parents are encouraged to participate in the intervention.

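### The programme is delivered in parent groups, but the mixed models name only within-subject correlation and the 54/70 sample size shows no clustering allowance; if change varies between groups, its standard errors are too small

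*Protocol article*

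**What the plan says.** Delivery is in groups. The intervention section of the Protocol article states "Each group includes parents from up to 10 families, i.e., in total 20 parents" and "Groups of Everyday Life and Parenting start four to six times every term". It lists discussion and peer support among the delivery components, with on-site or digital delivery according to parents' preference. Under Recruitment, only one parent per family can be a research subject, so a group contributes at most 10 analysed parents.

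The Background says that the effect of group parenting programmes depends partly on parents completing them, and adds: "This in turn is influenced by the group itself".

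The section Mixed-effects models analysis plans linear mixed models for ECBI, SDQ, MaaP, PSS and GHQ-12 at three time points and gives this reason: "Mixed-effects models are appropriate for repeated measures data as they account for within-subject correlations and can handle missing data". It does not list the random effects.

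The section Participants sizes this part of the study: "To be able to detect an effect size of 0.35 with an alpha of 0.05 and power of 80%, we will need at least 54" parents, and then "If we assume a 20% attrition rate, 70 participants will need to be recruited". It mentions no group size, intraclass correlation or design effect.

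Under Materials, the primary outcomes come from the weekly parent single-case data; the pre/post questionnaires are secondary.

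**The concern.** Parents who attend the same sessions, discuss the same material and support one another may change together. A model that knows only which measurements belong to which parent then counts each parent's change as independent information and reports a standard error that is too small.

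The component that matters is variance between groups in change (group-by-time). A group effect that is the same at every time point drops out of a change score, so a random intercept for group would not by itself deal with the problem.

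At stake are the intervals and p-values for five secondary questionnaire outcomes, which the article intends as its group-level findings and wants to compare with randomised studies. The health economic analysis inherits the issue if parents rather than groups are resampled.

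**Working it through.** **Reproducing 54 and 70.** The article does not give the test, its sidedness or the correlation over time, so several readings were tried. A one-group repeated-measures F test matches exactly, with f = 0.35/2 = 0.175, m = 3 time points and assumed ρ = 0.5:

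λ = f²·N·m/(1−ρ) = 0.030625 × 54 × 3 / 0.5 = 9.92, on 2 and 106 df; power 0.8004.

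A two-sided paired t test with 0.35 in raw SD units and ρ = 0.6 also gives 54. With 0.35 standardised by the SD of change, a paired t test needs 67 (two-sided) or 52 (one-sided). All these readings take parents as independent. For attrition, 54/0.8 = 67.5, so 68 against the stated 70; conversely 70 × 0.8 = 56. The margin is two parents.

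**Parents per group.** "The study will run from August 2024 to December 2025", which I take as three terms (assumption). Three terms × 4 to 6 starts = 12 to 18 groups. Spread evenly:
- 54 analysed: 54/18 = 3.0 to 54/12 = 4.5 per group
- 70 recruited: 70/18 = 3.9 to 70/12 = 5.8 per group

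That is about 3 to 6, with a ceiling of 10.

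**Effect of clustering.** Let k be the parents per group and ICC the intra-group correlation of change. The article gives no ICC; 0 to 0.10 is assumed.

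- Design effect: DE = 1 + (k−1)·ICC
- True over naive standard error: √DE
- Actual size of a naive 5% test: 2·[1 − Φ(1.96/√DE)]
- Power at 54 when grouping is allowed for: the F test above with λ/DE
- Parents needed: 54 × DE, rounded up

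| k | ICC | DE | SE ratio | Naive test size | Power at 54 | N needed |
|---|---|---|---|---|---|---|
| any | 0 | 1.00 | 1.00 | 5.0% | 80% | 54 |
| 3 | 0.02 | 1.04 | 1.02 | 5.5% | 78% | 57 |
| 3 | 0.05 | 1.10 | 1.05 | 6.2% | 76% | 60 |
| 3 | 0.10 | 1.20 | 1.10 | 7.4% | 72% | 65 |
| 4 | 0.05 | 1.15 | 1.07 | 6.8% | 74% | 63 |
| 4 | 0.10 | 1.30 | 1.14 | 8.6% | 68% | 71 |
| 6 | 0.02 | 1.10 | 1.05 | 6.2% | 76% | 60 |
| 6 | 0.05 | 1.25 | 1.12 | 8.0% | 70% | 68 |
| 6 | 0.10 | 1.50 | 1.22 | 11.0% | 62% | 81 |
| 10 (ceiling) | 0.10 | 1.90 | 1.38 | 15.5% | 51% | 103 |

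Worked line for k = 6, ICC = 0.10: DE = 1 + 5 × 0.10 = 1.50; √1.50 = 1.225; 1.96/1.225 = 1.60; size = 2·[1 − Φ(1.60)] = 0.110.

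The last two consequences are alternatives: a naive analysis pays in test size, a correct one in power. The power column keeps the original degrees of freedom, so it is slightly optimistic with few groups.

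**Simulation of the naive pre-post test.**
- 9 groups of 6: type I error 0.049 when groups differ only in level, 0.078 at a change ICC of 0.05, 0.109 at 0.10.
- 18 groups of 3: 0.051, 0.061 and 0.075.

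These agree with the formulas and confirm that a constant group effect does no harm.

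**The case against.** The strongest reply is that the article does not specify a random-effects structure at all. The sentence on within-subject correlation is a general reason for choosing mixed models, and a condensed article commonly leaves the model terms to an analysis plan, which is not shown here. That stands: a reader might infer that the planned models leave parenting group out, but the text neither includes nor excludes it. The sample size is different. It is a figure stated in the article, and no design effect accompanies it.

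Other stronger readings also fail:

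- **That the Background says outcomes depend on the group.** The sentence concerns programme completion, so the link to the effect is indirect. Discussion and peer support make shared change plausible but do not quantify it.
- **That leader effects separate the groups.** The article does not say which leaders run which groups.
- **That the standard errors are certainly too small.** This needs group-by-time variance, for which no figure is given. At zero there is no error.
- **That the inflation is large.** With 54 analysed parents over 12 to 18 groups there are 3 to 4.5 per group, the lower part of the table.
- **That the main results are at risk.** The primary outcomes are analysed participant by participant.
- **That the bootstrap resamples individuals.** The article does not name the resampling unit.

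**Conclusion.** The point holds as a conditional one. Treatment is given in groups, within-subject correlation is the only dependence named for the questionnaire models, and 54/70 carries no stated allowance for clustering. Analysed on that footing, the standard errors of change are too small whenever change varies between groups.

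Over the assumed range (3 to 6 parents per group, ICC of change 0.02 to 0.10), the understatement is small to moderate. For 4 parents per group and an ICC of 0.05, the true standard error is 7% larger, a nominal 5% test runs at 6.8%, and power is 74%. Even the mildest clustered case (3 per group, ICC 0.02) needs 57 parents, one more than the 56 that 70 recruits leave after 20% attrition.

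This rests on three recruiting terms, an even spread over groups, the same design effect for each time contrast, and the repeated-measures reading of 54. Fewer or uneven groups would raise the figures.

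**What to change.** - Record each participant's parenting group. The clinic presumably holds this, though the article does not say so.
- Include a group-by-time random effect in each questionnaire model, with Kenward–Roger or Satterthwaite degrees of freedom. If its variance cannot be estimated, use standard errors clustered on group with a small-sample correction.
- In the cost-effectiveness bootstrap, resample groups rather than individual parents.
- Restate the power of 54/70 under a stated ICC and group size. This is a matter of honest reporting for a secondary analysis and does not require enrolling more families.

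The cost is one identifier and one variance term. Intervals will be somewhat wider, and with 12 to 18 groups some fits will be singular; a variance estimated at zero should not then be read as proof that groups do not matter. If change does not vary between groups, the results will barely move.
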